Another essential feature of the application is a panel dedicated to reporting patients’ vital signs (blood pressure, heart rate, weight, saturation, and glycemia), which will be daily analyzed, and if necessary, a short message will be sent to the patient, advising to present to the primary healthcare clinic or emergency department. Patients will be instructed to report their parameters daily, in case of manually entered data. If the patient has a wrist-worn wearable device, compatible with ‘health; application on iOS or Android, then this data will also be presented in the afterAMI app. For instance, in the case of patients with smartwatches allowing for heart rate measurement with photopletyspography or ECG, these parameters (heart rate, blood pressure, body weight, saturation, and physical activity) will automatically be transferred into the app, directly after measurement. Patients with a pressure gauge without a connection to the mobile phone will have to enter the data manually. Naturally, there is room for error associated with adding the value of a particular parameter, but it can also happen during traditional “notebook” notes. A possible clinical scenario is the detection of an alarming rapid increase in bodyweight, which might foreshadow incoming heart failure exacerbation. Another potential use of the application is reporting rapid pulse. Then, new-onset atrial fibrillation might be suspected. In every case requiring medical confirmation, the patient will be referred to the nearest emergency room. However, all patients will be informed, that they should immediately present to the nearest emergency unit or contact the emergency services, in case of recurring angina or any other acute complaints.

Additionally, the application will send notifications with reminders to take drugs. This solution has been previously evaluated in many studies and proved to be a successful tool in increasing adherence to therapy [14].

Moreover, the application includes a module with air pollution parameters measured amidst the localization set up. If they exceed the alarming levels, the patients will be notified, and it will be suggested to minimize outdoor physical activities

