### Outcomes {12}, Participant timeline {13}, Plans to promote participant retention and complete follow-up {18b}

All 100 patients will be observed for 6 months after discharge. The endpoints will be assessed twice, during two control visits, in 1- and 6-months, after enrollment. Patients will be called to schedule the control visit’s date after discharge. Additionally, patients in the IG will receive a notification in their mobile app reminding them about the upcoming ambulatory visits.

Figure 2 shows the recommended SPIRIT figure with the participant timeline. Primary outcome includes both need for rehospitalization and/or urgent outpatient visit and assessed between baseline and 6-month control visit. There are five secondary outcomes related to cardiovascular risk factors control: blood pressure, body mass, nicotinism, dyslipidemia and need for rehospitalization and/or urgent outpatient visit assessed between baseline and 1-month control visit. Detailed target values regarding risk factors control have been presented in Table 1 based on ESC Chronic Coronary Syndrome guidelines [16]. Each value will be categorized as met or not. Secondary outcomes will also include quality of life and depression severity assessment (MacNew, EQ-5D-5L, and DASS-21 questionnaires), cardiovascular risk factors knowledge (CVD risk factors identification recommended BP values, desired lifestyle intervention identification). and return to work in case of professionally active patients.

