#### Secondary outcome measures

##### Cardiovascular risk factors

Blood pressure

All patients at discharge are asked to measure and note blood pressure values daily. The mobile application-derived mean blood pressure values covering 5 days prior to their visits will be averaged for the IG patients. The mean blood pressure values of CG-comprised patients will also be averaged, but based only on the presented written notes. Additionally, meeting guidelines-based recommended values will be checked in both groups. Hypertension is one of the main cardiovascular risk factors, with a significant prevalence of 1.13 billion worldwide [17]. Hypertension control in patients after MI is crucial and correlates with patients’ prognosis [18].

Body mass

All patients will be weighed on admission tl and during control visits 1 and 6 months after discharge. Weight change will be measured. Maintaining a healthy body weight is one of the fundamental aspects of preventing cardiovascular diseases and an essential treatment element after an MI.

Nicotinism

All patients will be asked about smoking on admission and during control visits 1- and 6-months after discharge. Smoking cessation is one of the main goals of patients after MI. Quitting smoking is necessary to reduce the risk of another ischemic incident. It has been documented that smoking cessation results in 50% reduction in the risk of experiencing another MI [19].

Dyslipidemia

All patients after MI will have their cholesterol levels measured during hospitalization. Subsequent cholesterol level measurements will be performed during control visits. According to ESC guidelines, different groups of patients have different LDL cholesterol target values, which should be met during the rehabilitation process [20]. Lowering LDL cholesterol levels correlates with a better prognosis after MI [21].

Quality of life

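### The secondary blood-pressure endpoint is read from app records in one arm and from patients' written notes in the other, so recording source is tied to allocation

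*Protocol article*

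**What the plan says.** The blood-pressure paragraph under Secondary outcome measures gives both arms one instruction: "All patients at discharge are asked to measure and note blood pressure values daily". It then names a different source for each arm. Intervention arm: "The mobile application-derived mean blood pressure values covering 5 days prior to their visits will be averaged for the IG patients". Control arm: "The mean blood pressure values of CG-comprised patients will also be averaged, but based only on the presented written notes".

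The Intervention description section gives two routes by which a value reaches the app. For patients with compatible equipment, "these parameters (heart rate, blood pressure, body weight, saturation, and physical activity) will automatically be transferred into the app, directly after measurement". Otherwise, "Patients with a pressure gauge without a connection to the mobile phone will have to enter the data manually". On recording error it says: "Naturally, there is room for error associated with adding the value of a particular parameter, but it can also happen during traditional “notebook” notes".

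The Outcomes section lists blood pressure among the risk-factor outcomes and adds: "Each value will be categorized as met or not". Table 1 sets a systolic target band 10 mmHg wide (120–130 mmHg in general, 130–140 mmHg above age 65). Under Statistical methods, secondary endpoints are assessed as change from baseline, and a patient with missing data is left out of the analysis concerned.

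**The concern.** Randomisation makes the arms comparable in who the patients are. It does not make an outcome comparable when it is read from a different record in each arm. Here the record is chosen by allocation, so a systematic difference between app records and presented notes has the same form in the data as a treatment effect. It could create a difference or hide one.

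Risk-factor management is part of the hypothesis stated under Objectives, and blood pressure is one of its measured components. An unexplained difference in this outcome would bear on one of the trial's main claims, even though the primary endpoint (rehospitalisation or urgent outpatient visit) does not depend on it.

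**Working it through.** **Step 1. The two arms side by side.**

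| Feature | Intervention | Control |
|---|---|---|
| Instruction | daily measurement and noting | the same |
| Source of endpoint value | app | written notes only |
| Window | 5 days before the visit | not restated |
| Entry route | automatic transfer or typed by hand | handwritten |
| Values seen by the team between visits | yes, analysed daily | none described |
| No record available | dropped from the analysis | dropped from the analysis |

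The first and last rows are common to the arms. The other four differ, or may differ, by allocation.

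**Step 2. Comparison with the other risk factors.** In the same section, body mass is weighed and cholesterol is measured at the control visits in both arms, and smoking is asked about in both arms in the same way. Of the four risk factors, only blood pressure has its source split by arm. The article describes no clinic reading, common source or sensitivity analysis for it.

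**Step 3. Does change from baseline remove the problem?** Not by itself. App access comes only with allocation, so a baseline taken before allocation cannot carry the app-specific part of an offset. That part stays in the follow-up value and so in the change.

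**Step 4. How large could it be?** The documents give no figure for this endpoint, neither an SD nor a difference between sources, so there is nothing to reproduce. What follows is an illustration on assumptions.

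- Assumed: SD 13 mmHg, 50 per arm (the 100 planned patients split equally), no true effect, two-sided 5% test.
- SE of the difference = SD × √(2/n) = 13 × √(2/50) = 2.6 mmHg.
- With an average arm offset b, the false-positive rate is P(Z > 1.96 − b/SE) + P(Z < −1.96 − b/SE).

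| b (mmHg) | b/SE | False-positive rate |
|---|---|---|
| 0 | 0 | 5.0% |
| 1 | 0.38 | 6.7% |
| 2 | 0.77 | 12.0% |
| 3 | 1.15 | 21.1% |
| 5 | 1.92 | 48.5% |

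Sensitivity to the assumed SD, at 50 per arm: over SD 12–18 mmHg, an offset of 2 mmHg gives 8.6–13.3%, 3 mmHg gives 13.3–24.0% and 5 mmHg gives 28.4–54.9%. At 38 per arm (the number before the allowance for dropout) the ranges are 7.7–11.2%, 11.2–19.3% and 22.8–44.3%.

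**Step 5. Dilution.** b is the average over the whole arm. If a 5 mmHg source difference affected only 25% of intervention patients (an assumption), then b = 0.25 × 5 = 1.25 mmHg, b/SE = 0.48, and the rate is 7.7%.

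**Step 6. Target attainment.** The band has two edges, so an offset can move patients in or out. Assuming an SD of 15 mmHg, the share inside 120–130 mmHg is 24.8% at a mean of 130 and 21.1% at a mean of 135. A 5 mmHg offset moves this proportion by 3.7 percentage points here, a milder distortion than for the mean.

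**The case against.** The strongest reply is that both arms do the same thing at home. They receive the same instruction, and no text says that the trial supplies a cuff or a wearable. Ownership of connected equipment precedes randomisation and should balance. A control may write down a smartwatch or connected-cuff reading, and an intervention patient with an unconnected gauge types in the kind of reading a control notes on paper. This stands. A reader might infer that the arms are measured with different devices, or that the intervention arm as a whole is fed by wearables, but the documents do not support that. What does differ is the recording channel, along with the opportunity for selecting entries and for gaps.

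Three further points narrow the concern.

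- The statement that control values are also averaged follows directly on the 5-day sentence, so a shared window is a natural reading. It is not stated, however, and the full protocol may settle it.
- The exclusion rule applies to both arms, so a patient with no app entries is lost as well. A reader might infer that loss must be greater among controls. The documents show only that it depends on a different record in each arm.
- The article acknowledges error in both app entry and notebooks. That does not show the two errors to be equal, which is what an unbiased comparison needs.

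On size, a reader might take the upper end of Step 4 as an estimate for this trial. It is not: the SD and the offset are assumed, and 5 mmHg would have to be the average over the whole arm. The SD of a change score may also differ from 13 mmHg.

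**Conclusion.** The concern holds in a limited form. The article fixes the recording source of the blood-pressure endpoint by arm and does not harmonise it elsewhere. An arm difference in mean blood pressure or in target attainment therefore cannot be attributed to the app's effect rather than to the record it was read from. That conclusion rests on the text alone.

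The size and direction of the bias cannot be derived from the documents. The illustrative false-positive rate of 6.7% to 48.5% depends on an SD of 13 mmHg, 50 per arm, no true effect and an average arm offset of 1 to 5 mmHg. If only a minority of patients is affected, the lower end is the relevant one. An offset in the opposite direction could mask a true benefit. The primary endpoint and its sample size are not touched. The point should be corrected, but it does not threaten the trial's main comparison.

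**What to change.** - **Main comparison.** Base it on a blood-pressure reading taken by the same method in both arms at the 1- and 6-month control visits. An automated device is preferable, because the physicians at these visits are unblinded. For visits already held, use readings on file where they exist.
- **Home averages.** Keep them as supportive, with the same 5-day window before the visit and the same minimum number of readings in both arms.
- **Reporting.** Give the number of patients and of readings used per arm. Where no common-source reading exists, state that the home-based comparison is confounded by recording source.
- **What not to add.** Excluding automatically transferred values could be enforced only in the intervention arm, because a control's notes need not show the device. It would introduce a new asymmetry.

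**Cost.** The visits already take place, so the burden is one reading and an amendment of the endpoint wording, made and dated before anyone looks at blood pressure by arm. There are three downsides. A visit reading reflects fewer days than a home average. It may carry observer effects in an open-label trial. It may also be missing for early visits, since the article mentions no clinic reading. The last could be substantial: recruitment began on 1 December 2020 and this version is dated 21 February 2022. At the stated rate of about 7 patients a month, roughly 8.7 × 7 ≈ 61 patients would have passed their 6-month visit by then and 13.7 × 7 ≈ 96 their 1-month visit. If few readings are on file, the explicit statement of confounding becomes the main remedy.

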### Sample size {14}

Currently, data regarding the achieved reduction of rehospitalizations or prelevance of urgent visits associated with mobile application use remains limited. Most previous studies were conducted on smaller populations. The sample calculation was based on Widmer and colleagues’ [5] study, considering rehospitalization and urgent ambulatory visits—comparing the effects of an online and smartphone-based program with standard rehabilitation on the mentioned endpoint. A 40% decrease in the primary endpoint was observed. Fifty percent of patients in the control group and 20% in the interventional arm were rehospitalized or visited the emergency department.

An online calculator (https://clincalc.com/) was used to determine the sample size, assuming the power of 80% and significance of 5%. A total of 76 patients (38 per group) were required. However, considering a possible lost-to-follow-up group and possible dropouts, a decision to recruit 100 patients was made. The reason for the dropout is lack of consent or inability to attend control visits or consent withdrawal.

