## Statistical methods

### Statistical methods for primary and secondary outcomes {20a}, Methods for additional analyses (e.g. subgroup analyses) {20b}, Methods in analysis to handle protocol non-adherence and any statistical methods to handle missing data {20c}, Interim analyses {21b}

In terms of the endpoints, we will look at the frequency of the events 6 months after the discharge, since we believe that due to randomization the groups will be similar at the beginning. No other (including no interim) analyses will be performed in the present study. Regarding secondary endpoints, the change from baseline will be assessed and the frequency of the events in case of rehospitalizations and/or urgent ambulatory visits after 1 month. The distribution of continuous variables will be estimated using the Shapiro-Wilk test. Continuous variables presented with normal distribution will be presented as mean values and standard deviations (SD). All continuous variables presented non-normal distribution will be demonstrated as median values and interquartile ranges. In the case of variables with a normal and non-normal distribution, the groups will be compared using the Student's t-test and the non-parametric Mann-Whitney U test. The comparison of qualitative variables between the groups will be performed using the Fisher exact test. In order to compare changes in the values of continuous variables over time, the analysis of variance will be performed. To compare the outcome of the patients, the Kaplan-Meier estimators will be utilized. For quantitative variables, the change from baseline will be assessed. Additionally, in order to diminish differences in sex and age related to group size, propensity score matching analysis will be performed as well. We also plan to conduct a subanalysis in the group of patients who attended rehabilitation, as well as in those who did not attend.

A per-protocol analysis will be performed after completing all of the follow-up visits. In the analysis, we will include all patients who meet inclusion criteria and sign informed consent regardless of the follow-up completion. Statistical calculations will be performed twice; after obtaining data from the first follow-up visit from all patients and after the final follow-up, 6 months after discharge. In case of missing data, patients will be excluded from the particular analysis.

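### The 80% power claimed for 38 patients per group does not hold for Fisher's exact test, the test the protocol names: it has 73% power there and needs 44 per group for 80%

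*Protocol article*

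**What the plan says.** The Sample size {14} section of the protocol article takes its event rates from an earlier study of a smartphone-based programme: "Fifty percent of patients in the control group and 20% in the interventional arm were rehospitalized or visited the emergency department". With 80% power and a 5% significance level, an online calculator gave the result: "A total of 76 patients (38 per group) were required". Neither the test behind that calculation nor its sidedness is given. The section then explains the planned total: "considering a possible lost-to-follow-up group and possible dropouts, a decision to recruit 100 patients was made". It states no expected dropout rate.

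The Outcomes {12} section defines the primary outcome as a yes/no event over 6 months (readmission and/or an urgent outpatient visit). The Statistical methods section says that event frequency at 6 months will be examined, and for categorical data it states: "The comparison of qualitative variables between the groups will be performed using the Fisher exact test". Kaplan-Meier estimators are mentioned too, but no log-rank or other time-to-event test is named. Patients with missing data are left out of the analysis concerned.

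**The concern.** A sample size and its power belong to a particular test. The requirement of 38 per group looks like the output of the usual large-sample formula for two proportions, whereas the test named for this kind of endpoint is Fisher's exact test. In groups of about 40, Fisher's test rejects well below its nominal 5% level and so needs more patients for the same power.

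Two statements depend on this. One is the 80% power attached to 76 evaluable patients. The other is the margin for losses: going from 76 required to 100 recruited tells the reader that 24 patients can be lost before power drops below target. Because patients with missing data are excluded, each loss reduces the evaluable number directly, so the size of that margin matters.

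**Working it through.** **Inputs.** From Sample size {14}: p1 = 0.50 (control), p2 = 0.20 (intervention), power 0.80, significance 0.05, 38 per group, 100 recruited. From Statistical methods: Fisher's exact test for categorical variables. Assumed: two-sided testing (sidedness is not stated) and equal groups.

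**Step 1: reproduce the protocol's figure.** Pooled normal approximation without continuity correction, with mean rate p̄ = 0.35:

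n = [z(0.975)·√(2·p̄·(1−p̄)) + z(0.80)·√(p1(1−p1) + p2(1−p2))]² / (p1−p2)²

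= [1.960·√0.455 + 0.842·√0.41]² / 0.09 = (1.3221 + 0.5389)² / 0.09 = 38.48 per group.

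Rounded to the nearest whole number this is the stated 38; rounded up it would be 39. Other versions do not give 38:

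- two-sided with continuity correction: 44.9, so 45
- two-sided, unpooled variance: 35.8, so 36
- one-sided: 31
- one-sided with continuity correction: 37

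**Step 2: exact power.** For each group size n, every pair of counts (i, j) was enumerated. The binomial probabilities under 0.50 and 0.20 were summed over the tables that the test rejects at p ≤ 0.05.

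| n per group | Uncorrected chi-square | Fisher, two-sided | Boschloo |
|---|---|---|---|
| 38 | 80.0% | 73.0% | 77.2% |
| 39 | 81.3% | 73.2% | 79.5% |
| 43 | 85.5% | 79.6% | 84.6% |
| 44 | 86.4% | 80.2% | 84.9% |
| 50 | 89.5% | 85.3% | 88.8% |

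Boschloo's test here uses the largest cut-off on the Fisher p-value whose maximum size over all common event rates stays at or below 5%.

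**Step 3: where the power goes.** With both groups at a common rate of 35%, Fisher's true size is 2.9% at 38 per group and about 3% at 44 and 50. Its maximum over all common rates at 38 per group is 3.0%. About two fifths of the nominal 5% is therefore unused. The uncorrected chi-square errs the other way: its maximum size at 38 per group is 5.8%.

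**Step 4: loss margin.** As written: 100 − 76 = 24 patients, or 24% of those recruited. With Fisher's test: 2 × 44 = 88 evaluable, and 100 − 88 = 12 patients, or 12%.

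**The case against.** The case on the other side has five parts.

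- **The origin of 38 is inferred.** No test is named for the sizing, so the uncorrected formula is a deduction from reproduction. That is right, but the 73% does not depend on it: it follows from Fisher's test, 38 per group and 50% against 20%.
- **No sentence ties Fisher's test to the primary endpoint by name.** True, and an unseen analysis plan might name another test. In the document as published, though, it is the only between-group test that fits a binary endpoint.
- **The planned 100 is adequate on the protocol's own rates.** This stands. Power is 85.3% with all 100 evaluable and stays at about 80% down to 88. The 73% applies only if all 24 spare patients are lost, and nothing in the protocol predicts losses above 12%.
- **The protocol never states a 24% dropout rate.** Correct. It is the margin implied by going from 76 to 100, but no other margin is offered to the reader.
- **Uncertainty in the event rates matters more.** The section also speaks of a 40% decrease. Read as a relative fall (50% to 30%), the same formula would ask for 93 per group. That is a separate and larger question, and it does not make the stated power right for the stated rates.

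**Conclusion.** The point holds. At the evaluable number the protocol calls sufficient, the test it names has 73.0% power for 50% against 20%, so the type II error is 27% rather than 20%. Eighty per cent power needs 44 per group, 12 more evaluable patients than stated, which halves the implied loss margin from 24 to 12. This assumes two-sided testing at 5%, equal groups, and Fisher's test as the primary comparison. A one-sided Fisher test at 5% would give 83.3% at 38 per group, but the protocol states no one-sided test.

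The 38 is not an arithmetic slip, since it reproduces from a standard formula. The fault is that the sizing and the named analysis do not match. The practical effect is moderate: it bears on what retention the trial must achieve, not on whether 100 evaluable patients are enough under these rates.

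**What to change.** Name the test behind the sample size, name the primary test explicitly, and make the two agree. Either of these would do:

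1. Keep Fisher's exact test and restate the requirement as 88 evaluable patients (44 per group) for 80% power, so that recruiting 100 allows 12% loss.
2. Name Boschloo's unconditional exact test for the primary endpoint. It holds the 5% level and is never less powerful than Fisher's. Quote its power across the plausible evaluable range: 77.2% at 38, 84.9% at 44 and 88.8% at 50 per group. It still falls short of 80% at 38, so the 76-patient statement needs rewording here too.

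Switching to the uncorrected chi-square would recover the stated 80% at 38 per group, but its size can reach 5.8% there, so it is the weaker choice.

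The cost is one sentence in the sample-size or analysis section. No extra patients are needed, and the only loss is a less generous stated dropout margin. Any change of test should be fixed and dated before outcome data are analysed by group.
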